### Objectives

#### Primary objectives

Evaluate ACT’s efficacy in enhancing PTG among head and neck cancer patients compared to MBSR and a control (treatment-as-usual) immediately after the eight-week intervention and 24 weeks post-intervention compared to pre-intervention

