### Randomization

This study will use stratified permuted block randomization, stratifying trial participants according to their age (*18 to 40 years old*, *41 to 60 years old*, and *over 60 years old*) and gender (*male* and *female*). Participants will be randomized into three groups: an ACT group, an MBSR group, and a control group of patients on treatment-as-usual for intervention. Using a 1:1:1 allocation ratio and block randomization, we will randomly assign participants to the three groups. An allocation sequence will be generated via computer-generated random numbers, which will be obtained by a research assistant who is not otherwise involved in this study. The allocation sequence will be concealed in an opaque, sequentially numbered envelope.

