### Interventions

An eight-week psychosocial intervention will be administered to participants in each intervention group (MBSR and ACT) while participants in the control group will receive treatment-as-usual. The study’s outcomes will be assessed at three times: pre-intervention (t_0_), immediately after the eight-week intervention (t_1_), and 24 weeks after the intervention (t_2_).

Both the ACT and MBSR interventions will comprise eight sessions delivered at a rate of one session per week. Each session will last for one hour. At AMDI, USM, and UKMMC, chemotherapy for head and neck cancer lasts for 8 weeks, delivered at a rate of one session per week. Similarly, radiotherapy for head and neck cancer lasts for eight weeks at these institutions. Therefore, this study’s ACT and MBSR sessions will align with participants’ chemotherapy or radiotherapy sessions to ensure that all participants attend their intervention sessions. ACT and MBSR will be provided in group settings with intervention groups of 10 participants each.

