### Data analysis

All of this study’s data analysis will be conducted using the Statistical Package for Social Sciences, version 26 (SPSS 26; SPSS Inc., Chicago, Illinois, USA). Initially, the baseline sociodemographic and tumor characteristics will be presented by randomized groups (ACT, MBSR, and control groups).

The mean difference in the primary outcome (total PTGI-SF score) for the three randomized groups (ACT, MBSR, and control groups) at each specific time point (pre-intervention [t_0_], post-treatment at 8 weeks [t_1_] and 24 weeks after intervention [t_2_]) will be assessed using one way analysis of variance (ANOVA) followed by false discovery rate adjustment. For the main pool analysis, mixed linear model will be employed for comparing the primary outcome (total PTGI-SF score) between ACT and control groups and between MBSR and control groups across the three time points (t_0_, t_1_ and t_2_), while controlling for stratification factors such as age and gender. The main effects of intervention in the groups and time points will be presented as estimated marginal mean and standard error of mean. The study’s primary analysis will follow the intention-to-treat (ITT) principle. The data analysis for the study’s secondary outcomes (quality of life, hope, optimism, depression, anxiety, and EA) will be conducted similarly to the primary outcomes’ calculation. In addition, 95% confidence interval will also be presented alongside the main effect. Statistical significance will be two-tailed and set to *p* < 0.05.

To handle any missing data, if the missing data represent less than 5% of the study’s total collected data, they will be ignored. If the missing data represent more than 5% but less than 40% of the total collected and are assumed to be randomly missing, then multiple imputation (restricted maximum likelihood estimation) will be performed using Stata 15. However, if the missing data represent more than 40% of the total collected data or are assumed to be missing either not randomly or completely randomly, then only the collected data will be used for the study’s analysis, and the missing data will be explained as a research limitation in any publications of the study’s findings [68].

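### The per-visit ANOVAs of PTGI-SF use neither the baseline score nor the randomisation strata, and the mixed model as worded may use the baseline only in part, so precision that costs almost nothing is left unused

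*Protocol article*

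**What the plan says.** Table 1 of the protocol article schedules PTGI-SF, the primary outcome, at t0, t1 and t2. The Data analysis section then names two analyses.

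- **Per-visit comparison.** The mean difference between the three arms at each time point, t0 included, "will be assessed using one way analysis of variance (ANOVA) followed by false discovery rate adjustment". No covariate is named, and a one-way ANOVA has none.
- **Main pooled analysis.** A mixed linear model compares ACT with control and MBSR with control "across the three time points (t_0_, t_1_ and t_2_), while controlling for stratification factors such as age and gender". The pre-intervention score is thus one of three repeated responses. On reporting, the section says: "The main effects of intervention in the groups and time points will be presented as estimated marginal mean and standard error of mean".

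The secondary outcomes are to be analysed in the same way. The Randomization section describes permuted blocks, "stratifying trial participants according to their age" in three bands and gender. The primary objective asks for efficacy "immediately after the eight-week intervention and 24 weeks post-intervention compared to pre-intervention".

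**The concern.** The baseline PTGI-SF is probably the best single predictor of the later scores, and every patient is due to provide it. The t1 and t2 ANOVAs ignore it, although the primary objective is framed relative to pre-intervention. They also ignore the age and gender strata that the randomisation balances. Any chance difference between arms at t0 carries into those comparisons in proportion to the correlation, and the residual variance is larger than it need be.

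The mixed model is a different case, because it does contain t0. How much it gains depends on how the t0 means are handled. With a free t0 mean in each arm, the natural contrast is the difference in change from t0, which is less precise than a baseline-adjusted contrast. With a common t0 mean, nothing is lost. The article does not say which is meant, and it speaks of main effects over time points that include one before treatment.

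Precision is at stake in a trial of 120 patients that expects 30% drop-out, on the primary outcome and on every secondary scale analysed the same way.

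**Working it through.** **Inputs from the protocol article (Participants, Interventions, Randomization).** Effect size 0.15, two-tailed alpha 0.05, power 0.8, three equal groups, 93 evaluable, 120 randomised; three assessments; strata of three age bands and two genders.

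**Assumption.** The article gives no baseline-to-follow-up correlation rho. I use 0.5, with a range of 0.3 to 0.7, equal variances and the same correlation between all visits.

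**1. The plan's own figure.** The article says only that G-Power was used for ANOVA. The 93 is recovered as a repeated-measures within-between interaction with k = 3 groups, m = 3 measurements and rho = 0.5:

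- lambda = N f² m / (1 − rho) = 93 × 0.0225 × 3 / 0.5 = 12.56
- df = (k − 1)(m − 1) = 4 and (N − k)(m − 1) = 180
- power = 0.811; N = 90 gives 0.796, so 93 is the smallest multiple of three that reaches 0.80.

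This shows that 0.5 fits the sample-size calculation. It does not show that 0.5 is the correlation of PTGI-SF in these patients.

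**2. Relative variance of a pairwise arm contrast at one follow-up visit.**

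- Unadjusted ANOVA: 1
- Change from t0, free t0 means: 2(1 − rho)
- Baseline as covariate, or t0 as response with equal t0 means: 1 − rho²

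| rho | ANOVA | Change from t0 | Baseline-adjusted | Saving vs ANOVA | Saving vs change |
|---|---|---|---|---|---|
| 0.3 | 1.00 | 1.40 | 0.91 | 9% | 35% |
| 0.4 | 1.00 | 1.20 | 0.84 | 16% | 30% |
| 0.5 | 1.00 | 1.00 | 0.75 | 25% | 25% |
| 0.6 | 1.00 | 0.80 | 0.64 | 36% | 20% |
| 0.7 | 1.00 | 0.60 | 0.51 | 49% | 15% |

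A generalised least squares calculation with three visits gives the same variances. It also confirms that the model with equal t0 means attains 1 − rho² exactly.

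**3. Power of the per-visit ANOVA, f = 0.15.** Unadjusted lambda = N f²; adjusted lambda = N f² / (1 − rho²). At rho = 0.5:

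- N = 93: lambda 2.09 becomes 2.79; power 0.228 becomes 0.293.
- N = 120: lambda 2.70 becomes 3.60; power 0.286 becomes 0.370.

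At N = 93 the gain is about 2 points at rho = 0.3, 4 at 0.4 and 11 at 0.6. Charging four degrees of freedom for baseline and strata changes these powers by less than 0.001.

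**4. Power of the group-by-time test behind the 93, rho = 0.5.** The two changes from t0 have covariance (1 − rho)(I + J), where I is the identity and J the 2 × 2 matrix of ones. The two baseline-adjusted follow-ups have covariance (1 − rho)(I + rho J). The inverse of I + aJ is I − [a/(1 + 2a)]J.

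- Equal effect at both visits: 2 − 4a/(1 + 2a) is 0.667 for a = 1 and 1.000 for a = 0.5; ratio 1.5. Lambda 18.83, power 0.947.
- Effect at one visit only: 1 − a/(1 + 2a) is 0.667 and 0.750; ratio 1.125. Lambda 14.12, power 0.860.

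The starting power is 0.811 in both cases. At rho = 0.7 the ratios shrink to 1.25 and 1.06; at rho = 0.3 they are 1.875 and 1.22.

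**5. A pairwise contrast with 0.80 power unadjusted at one visit** reaches 0.84, 0.86, 0.90, 0.94 and 0.98 with baseline adjustment at rho = 0.3, 0.4, 0.5, 0.6 and 0.7.

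**The case against.** The strongest reply is that the main analysis already contains the baseline. The pooled model takes t0 as a response and adjusts for age and gender. If its t0 means are constrained equal, the loss is 0% at every rho, and the published sentence does not rule that out. The article is a condensed account and refers to a statistical analysis plan that is not shown; the group-by-time term and any t0 constraint may be set there. This stands, so silence on those terms is not itself an error.

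A second reply is that leaving out the baseline causes no bias in a randomised comparison, and that the test which reproduces 93 has power 0.81 without it. This also stands: the point is about efficiency, not validity, and it does not show that the planned power fails.

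The replies do not reach the per-visit comparisons. One-way ANOVA is a stated method, not an omitted detail, and it excludes both the baseline score and the strata. Reporting main effects over time points that include t0 is also a stated choice, and it sits poorly with an objective framed against pre-intervention.

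**Conclusion.** The point holds in a limited form. For the t1 and t2 ANOVAs the loss is definite whenever rho differs from zero: the contrast variance could be 9% to 49% lower for rho of 0.3 to 0.7. For the mixed model it is conditional: 35% to 15% lower than a change contrast with free t0 means, and nothing if the t0 means are already equal. All of these rest on a correlation that the article does not give.

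Three stronger readings are tempting and are not supported.

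- **A fixed 25% loss in both analyses.** The agreement at 25% is a coincidence at rho = 0.5; away from it the two savings move in opposite directions. Even at 0.5, the group-by-time test with an effect at one visit gains a factor of only 1.125 in lambda.
- **The main model ignores the baseline, so every confidence interval is too wide and carries the baseline imbalance.** The model includes t0, and a change-from-t0 contrast removes a baseline difference.
- **The treatment effect will be averaged over all three visits.** Taken literally, a group main effect over t0, t1 and t2 would shrink a constant post-baseline effect to two thirds. The sentence may equally mean marginal means by arm and visit, so the wording needs clarifying and does not prove dilution.

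The change is worth making before unblinding, because the gain is real and nearly free.

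**What to change.** In the Data analysis section:

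1. Fit the mixed model to PTGI-SF at t1 and t2 with arm, visit, arm-by-visit, baseline PTGI-SF, baseline-by-visit, age stratum and gender. Alternatively, keep t0 as a response and constrain the t0 means to be equal across arms. Use one or the other, so that t0 is not both response and covariate.
2. Report the arm contrasts at t1 and at t2 from this model, in place of main effects over time points that include t0.
3. Replace the t1 and t2 one-way ANOVAs by ANCOVA with baseline PTGI-SF, age stratum and gender.
4. Do the same for each secondary scale, with its own t0 score.

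Dropping the t0 ANOVA, which tests a difference that randomisation already makes due to chance, is optional.

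The cost is wording and a few lines of code. With the baseline as a covariate, the mixed model spends two degrees of freedom on baseline terms and each ANCOVA one, plus three for the strata (two for age, one for gender). No patients, visits or data are added.

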### Participants

This study’s participants will be recruited from the source population. This population includes all newly diagnosed head and neck cancer patients who have been treated only with surgery or who have not yet received treatment and who are registered under the oncology and otorhinolaryngology unit of the Advanced Medical and Dental Institute (AMDI) at the Universiti Sains Malaysia (USM) or the oncology and otorhinolaryngology unit of Universiti Kebangsaan Malaysia Medical Centre (UKMMC). The study’s sample size was determined based on G-Power 3.1.9.2 for analysis of variance (ANOVA). This sample size was calculated based on continuous responses to the posttraumatic growth inventory used in the study by Labelle et al. (2015) [48] with a medium effect size (0.15) and a two-tailed alpha of 0.05. The results of this calculation indicated that the current study requires a total sample of 93 for three equal-sized groups to achieve a power of 0.8. Anticipating a drop-out rate of 30%, we estimated a total sample size of 120 respondents and 40 respondents for each group.

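### The Data analysis section names no contrast for change from baseline: it reports main effects over t0 to t2, which dilute the treatment effect, while the 93 matches a group-by-time interaction

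*Protocol article*

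**What the plan says.** Under Primary objectives, ACT is to be compared with MBSR and control on PTG right after the eight-week programme and at "24 weeks post-intervention compared to pre-intervention". That is a between-arm comparison of change.

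Under Data analysis, total PTGI-SF in the three arms at t0, t1 and t2 "will be assessed using one way analysis of variance (ANOVA) followed by false discovery rate adjustment". A mixed linear model then compares ACT with control and MBSR with control over the three time points, controlling for age and gender. The output of that model is described in one sentence: "The main effects of intervention in the groups and time points will be presented as estimated marginal mean and standard error of mean". A later sentence adds a 95% confidence interval next to the main effect. Neither an interaction nor a change from t0 is mentioned.

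Under Participants, the sample size comes from G*Power for an ANOVA, "with a medium effect size (0.15) and a two-tailed alpha of 0.05", and the trial "requires a total sample of 93 for three equal-sized groups to achieve a power of 0.8". The type of ANOVA, the number of measurements and the correlation between visits are not given.

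**The concern.** The objective, the sample size and the analysis appear to refer to different effects. The objective is a difference in change. The sample size looks like that of a group-by-time interaction. The analysis names tests at single visits and main effects.

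If a statistician follows the Data analysis section literally, the primary treatment estimate averages the post-treatment differences with a t0 difference that has expectation zero. The estimate is pulled towards zero, and t0 is spent as a response instead of being used to reduce variance. The one-way ANOVA at t0 tests a null hypothesis that randomisation already makes true, yet it is one of the visit tests to which the false discovery rate adjustment is attached. The stated power of 0.8 would then not describe the test that is run.

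**Working it through.** **Inputs.** From Participants: effect size 0.15 (taken as Cohen's f), alpha 0.05, power 0.8, three equal groups, N = 93. From Interventions: three measurements. Assumed, because not stated: correlation r = 0.5 between any two visits, and sphericity. All powers are for the three-group F test, from the noncentral F distribution with noncentrality λ.

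**1. Reproducing 93.** For the group-by-time interaction, λ = f² × N × 3/(1 − r), with 4 and 2(N − 3) degrees of freedom.
- N = 93: λ = 0.0225 × 93 × 3/0.5 = 12.56, power 0.811.
- N = 90: λ = 12.15, power 0.796.

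So 93 is the smallest multiple of three that reaches 0.8. The match depends on r: the same formula gives 129 at r = 0.3 and 57 at r = 0.7. Other readings at f = 0.15 do not give 93: one-way ANOVA 432, group main effect over three visits 291, time main effect 75. Reading 0.15 as f² gives 69, 48 and 18 for one-way, group main effect and interaction.

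**2. Dilution.** If two arms differ by 0 at t0 and by δ at t1 and at t2, the group main effect estimates (0 + δ + δ)/3 = 2δ/3. This needs no power assumption.

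**3. Power under one common pattern of means.** Let the arms be equal at t0 and separated by the same amounts at t1 and t2. The visit profile (0, 1, 1) has mean 2/3 and deviations (−2/3, 1/3, 1/3), whose mean square is (4/9 + 1/9 + 1/9)/3 = 2/9. Hence:
- f² at a post-baseline visit = 0.0225/(2/9) = 0.10125, so f = 0.318
- f for the group main effect = (2/3) × 0.318 = 0.212

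At N = 93 and r = 0.5:

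| Test | λ | Power |
|---|---|---|
| Interaction | 12.56 | 0.81 |
| One-way ANOVA at t1 or t2, λ = N × 0.10125 | 9.42 | 0.78 (0.62 at alpha 0.05/3) |
| Group main effect over t0 to t2, λ = N × 3 × 0.212²/(1 + 2r) | 6.28 | 0.59 |
| Average of t1 and t2 adjusted for t0, λ = N × 0.10125/[(1 + r)/2 − r²] | 18.83 | 0.98 |

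The alpha of 0.05/3 is a strict stand-in for the false discovery rate adjustment. With 84 completers (120 × 0.7), the last three rows become 0.73 (unadjusted), 0.54 and 0.96.

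**4. Information.** The adjusted average carries 18.83/6.28 = 3 times the information of the group main effect at r = 0.5. The ratio is 2.1 at r = 0.3 and 5 at r = 0.7. At a single visit, adjusting for t0 gives 1/(1 − r²) = 1.33 times the information of the unadjusted ANOVA at r = 0.5.

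**The case against.** The best defence is that the wording is loose rather than wrong. Marginal means for groups and time points can come from a model with a group-by-visit term, the objectives speak of comparison with pre-intervention, and the Blinding section refers to a statistical analysis plan that is not shown. A full list of model terms is normally left to such a plan. This stands in part: the article does not exclude an interaction, so it cannot be said that the diluted effect will certainly be the primary result. But the article does more than leave terms out. It names the effect to be presented, twice, and that effect is not the one in the objective.

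A reader might also infer that the planned tests have power of only 0.23 (one visit) and 0.33 (group main effect) at 93, or that 432 or 291 patients are needed. Those figures follow only if the same nominal f = 0.15 is put into each test. An interaction f of 0.15 is a different pattern of means from a main-effect f of 0.15. Carried through consistently, the figures are 0.78 and 0.59, and the unadjusted visit test is close to 0.8.

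Finally, the link between 93 and the interaction is a reconstruction. The match is exact, but r and the ANOVA type are inferred, and only the sponsor can confirm them.

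**Conclusion.** The point holds as a mismatch between the objective and the effect named for analysis. The two-thirds dilution follows from the text as written, with equal expected means at t0 and a constant effect at t1 and t2. Under that pattern, with r = 0.5 and sphericity, the named group main effect has power of about 0.59 at 93, some 20 points below the stated 0.8. The visit tests have 0.78 before multiplicity adjustment and 0.62 at the strict level, and a baseline-adjusted average of t1 and t2 has about 0.98. The 0.98 belongs to the averaged contrast, not to separate tests at t1 and t2.

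The documents do not support saying that the trial is too small, or that 93 was wrongly computed. If the sponsor already intends a group-by-visit contrast, the correction is one of wording. If not, the primary estimate would be biased towards zero.

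**What to change.** In Data analysis:
- Make one model primary: a mixed model for total PTGI-SF with visit, group-by-visit, and the age and gender strata. Handle baseline either as a covariate with t1 and t2 as responses, or by a common t0 mean across arms.
- Report between-group differences at t1 and at t2 relative to t0, with 95% confidence intervals, in place of main effects over all three visits.
- Drop the significance test at t0 and make the per-visit ANOVAs descriptive.

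In Participants, the sponsor should confirm and state the type of ANOVA, the number of measurements and the correlation behind 93. The interaction with r = 0.5 should not be written in unless the sponsor confirms it.

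The cost is wording only. No patients, visits or questionnaires are added, because PTGI-SF is already collected at t0, t1 and t2. The change should be made before unblinded data are seen.

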#### Other measures

The participants compliance to the interventions will be recorded as they will be requested to fill in electronic dairies regarding their performance of the home assignments and practice of the interventions at home. The reasons for absence from therapy sessions, dropouts and loss to follow up (such as loss of interest to participate, dislike of the intervention, not feeling well or death) will also be recorded.

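### The missing-data rule switches method on a whole-study percentage and an untestable assumed mechanism, and treats data missing not at random as if they were missing completely at random

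*Protocol article*

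**What the plan says.** All of the rule is in the last paragraph of Data analysis. It has three branches.

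- Low: "if the missing data represent less than 5% of the study’s total collected data, they will be ignored".
- Middle: if the missing data are "more than 5% but less than 40% of the total collected and are assumed to be randomly missing, then multiple imputation" is used. The method is given as "multiple imputation (restricted maximum likelihood estimation) will be performed using Stata 15".
- Fallback: "if the missing data represent more than 40% of the total collected data", or if they "are assumed to be missing either not randomly or completely randomly, then only the collected data will be used", and "the missing data will be explained as a research limitation in any publications of the study’s findings".

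The percentage is not tied to an outcome, a visit or an arm.

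The same section plans two analyses of PTGI-SF: a one-way ANOVA at each of t0, t1 and t2, and, as the main analysis, a mixed linear model across the three visits. It adds: "The study’s primary analysis will follow the intention-to-treat (ITT) principle".

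Three other places bear on the point. Participants anticipates 30% drop-out. Other measures will record reasons for loss such as "loss of interest to participate, dislike of the intervention, not feeling well or death". Support and ethics says that information from participants who withdraw will not be used, and Recruitment process says that it will be discarded.

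**The concern.** Four features of the rule are badly set.

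1. **Two opposite mechanisms share one branch.** Under MCAR, analysing what was collected is unbiased. Under MNAR it is not, and a limitation statement does not show how far the result could move.
2. **The denominator is too wide.** Baseline is normally near complete, and counting it dilutes losses that fall at t2 or in one arm, where the treatment comparison is made.
3. **The choice of method stays open.** Above 5%, whether to impute depends on which mechanism is assumed. Observed data cannot separate missing at random (MAR) from MNAR, and the article names no basis for the assumption.
4. **Two methods are merged.** Restricted maximum likelihood (REML) estimates the parameters of a mixed model. It does not describe multiple imputation, so the middle branch cannot be carried out as written.

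At stake is the t1 and t2 comparison of PTGI-SF. Some recorded reasons for loss, such as dislike of the intervention or feeling unwell, may plausibly relate to the outcome and differ between arms.

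**Working it through.** **Threshold arithmetic.** Inputs: 120 participants, 40 per arm (Participants); three assessments (Table 1). Assumption: the percentage is counted on total PTGI-SF scores, with baseline complete.

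- Planned scores: 120 × 3 = 360.
- 5% of 360 = 18 scores, so 17 missing scores fall below the threshold: 17/360 = 4.7%. Counted against scores actually collected, 17/(360 − 17) = 17/343 = 4.96%, still below 5%.
- If all 17 are at t2: 17/120 = 14% of that visit. If all are in one arm: 17/40 = 42.5% of that arm at t2.
- 40% of 360 = 144 scores, which is 144/240 = 60% of all post-baseline scores.
- The anticipated 30% drop-out is 36 participants. Lost at t2 only: 36/360 = 10%. Lost at t1 and t2: 72/360 = 20%. Both fall in the middle band.

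**Size of bias under MNAR.** The documents give no figures for this, so all inputs are assumptions: 30% of one arm missing at t2; probability of loss logistic in the t2 score, with lower scores more often missing; log-odds 0.5 or 1.0 per SD; SD 1; correlation 0.5 between any two visits; t0 and t1 complete; no outcome-related loss in the comparator.

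*Observed t2 mean (per-visit ANOVA).* Setting the logistic intercept to give 30% loss and integrating over the normal distribution, the mean of those observed is +0.143 SD (log-odds 0.5) or +0.253 SD (log-odds 1.0). The true mean is 0. The variance v among those observed is 0.954 or 0.860.

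*MAR-based estimate using t0 and t1.* Among those observed, each earlier visit has mean 0.5 × shift, variance 0.75 + 0.25v, covariance with the other earlier visit 0.25 + 0.25v, and covariance with t2 0.5v. By symmetry both regression coefficients equal b = 0.5v/(1 + 0.5v). Predicting t2 for everyone leaves a bias of shift − 2 × b × 0.5 × shift = shift × (1 − b).

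| Log-odds per SD | Observed-mean shift | v | b | MAR-based shift |
|---|---|---|---|---|
| 0.5 | 0.143 | 0.954 | 0.477/1.477 = 0.323 | 0.143 × 0.677 = 0.097 |
| 1.0 | 0.253 | 0.860 | 0.430/1.430 = 0.301 | 0.253 × 0.699 = 0.177 |

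So the shift is about 0.14 to 0.25 SD for the per-visit mean, and about 0.10 to 0.18 SD for an estimate that borrows from earlier visits. The second is smaller but not zero.

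**The case against.** The best defence is that the main analysis is already a mixed model. Fitted to collected data only, it naturally uses every observed visit and is valid under MAR. For that model the fallback is close to what a reviewer would ask for. This stands, and it limits the point in four ways.

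- A reader might infer that the fallback biases the primary estimate by 0.14 to 0.25 SD. The documents do not support that. The figure is a one-arm shift in observed means and belongs to the per-visit ANOVA; similar loss in other arms would partly cancel in a contrast. If loss depends only on the observed t1 score, the MAR-based shift is about zero.
- A reader might infer that imputing in the MNAR branch would have cured the bias. Standard imputation assumes MAR and would not.
- A reader might infer that the expected drop-out would simply be ignored. At 30% lost at t2, or at both follow-up visits, 10% to 20% of scores are missing and the low branch does not apply.
- A reader might infer that the trial has no MNAR sensitivity analysis, or that the mechanism will be chosen with the results in view. The Blinding section says that a statistical analysis plan is set before final unblinding and that independent statisticians do the analysis. That plan is not shown and may settle both. One can say only that the rule as stated contains no such analysis and names no basis for the assumed mechanism.

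The defence does not rescue the rule itself. The article states it in full, and it still joins MNAR to MCAR, uses a denominator blind to visit and arm, and misdescribes the imputation. The per-visit ANOVA on observed cases has no protection from the mixed model.

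**Conclusion.** The point holds as a fault in a stated rule, and it should be corrected. The 5% trigger can pass over a loss of 14% at t2, or 42.5% of one arm at t2, counting PTGI-SF scores with complete baseline. Under assumed MNAR, the rule offers collected data and a limitation statement, which leaves the possible bias unquantified. With 30% outcome-dependent loss in one arm and log-odds of 0.5 to 1.0 per SD, that bias is about 0.14 to 0.25 SD for per-visit observed means. It is about 0.10 to 0.18 SD for a MAR-based estimate at correlation 0.5. These are illustrations under assumed values, not predictions for this trial. The effect size of 0.15 in Participants is an ANOVA quantity whose scale the article does not define, so it should not be set beside them.

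**What to change.** 1. Remove the percentage and mechanism switches. Make the mixed model, fitted by REML to all observed visits of all randomised participants, the primary analysis whatever the percentage missing.
2. Take the t1 and t2 contrasts from that model rather than from per-visit ANOVA on observed cases.
3. Replace the MNAR branch with a prespecified sensitivity analysis: delta-adjusted or reference-based multiple imputation, informed by the recorded reasons for loss, reporting the shift at which the conclusion changes. Handle deaths separately, since imputing growth scores after death is not obviously meaningful.
4. Report missingness by arm and visit.
5. Delete restricted maximum likelihood as the description of the imputation.
6. Reconcile the statements in Support and ethics and in Recruitment process with the intention-to-treat statement, for example by keeping data collected before withdrawal where consent allows. Otherwise item 1 cannot be delivered.

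The cost is protocol or analysis-plan wording and a few extra model runs. Item 6 may also need a change to the participant information and ethics notification. No added patients or assessments are needed.
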